#### Missing Data

Missing data will be imputed using full information maximum likelihood. As with most longitudinal studies, participants leave the study at different times, with attrition commonly increasing over time. Traditional methods of handling missing data require the researcher to discard data or impute unknown values, which frequently causes estimation bias and loss of statistical power. These missing data concerns are ameliorated when using full information maximum likelihood, as it does not have the same limitations as other more common approaches (eg, listwise deletion and regression imputation methods).

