#### Statistical Models

##### Aim 1

Primary outcome data will be analyzed in Aim 1. For each of the 3 outcomes in Aim 1 (Dietary Quality Score and Food Security), at 3-month and 6-month periods, a 2-level multilevel model (MLM) will be constructed that examines change over time for individual participants within centers. MLMs consider that participants within a cluster (eg, a center) share characteristics that make them more like each other than participants at other centers. MLM has several distinct advantages over other modeling strategies: (1) MLM has greater statistical power given that the estimated standard errors are corrected for model dependency; (2) there is no need to assume or test for the homoscedasticity or sphericity assumptions, as these variance and covariance components are estimated within the MLM model. Depending on model complexity and whether the statistical assumptions are met, the models will be estimated via Bayesian estimation or maximum likelihood estimation with robust standard errors. For Level 1 (participant level), the outcome variable of interest will be modeled using pretest score on the outcome measure, treatment status (ie, control or experimental), and any nonequivalent baseline participant characteristics as covariates. Level 2 (center level) will model the cluster effect of centers on outcomes.

##### Aim 2

Data collected for Aim 2 represent our secondary research questions (eg, physical activity, technology knowledge and attitudes, social isolation, and loneliness). Data collected at all time points (Physical Activity Scale for the Elderly [PASE], technology knowledge and attitudes, social isolation, and loneliness) will be analyzed using MLM described in Aim 1. To minimize participant fatigue, data for this secondary research aim will be collected at defined intervals (T0, T1, and T2). These data will include the Healthy Eating Index and Short Physical Performance Battery (SPPB) to assess physical function. Differences between groups will be assessed at T2 for each outcome via 2-level covariate MLM models. Level 1 (participant level) will test whether treatment status (ie, control or experimental), pretest score on dietary quality, and food security, and any nonequivalent baseline participant characteristics predict outcomes. At Level 2 (center level), we will model the influence of the 7 centers.

##### Aim 3

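### Aim 1 relies on full information maximum likelihood for dropout, but its two-level model has no occasion level or participant random effect, so a missing outcome gains nothing from it as specified

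*Protocol article*

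**What the plan says.** The Missing Data section states: "Missing data will be imputed using full information maximum likelihood". It notes that attrition usually grows over time, and it contrasts the method with listwise deletion and regression imputation: "These missing data concerns are ameliorated when using full information maximum likelihood, as it does not have the same limitations" as those approaches.

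Under Statistical Models, Aim 1, the outcomes "at 3-month and 6-month periods" are to be analysed as follows: "a 2-level multilevel model (MLM) will be constructed that examines change over time for individual participants within centers". The levels are then fixed.

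- Level 1: "For Level 1 (participant level), the outcome variable of interest will be modeled using pretest score on the outcome measure, treatment status", plus baseline characteristics found to differ between cohorts.
- Level 2: "Level 2 (center level) will model the cluster effect of centers on outcomes".
- Estimation: "the models will be estimated via Bayesian estimation or maximum likelihood estimation with robust standard errors".

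The Aim 1 text gives no time term, no occasion level, no participant random effect and no auxiliary variable. It does not say whether months 3 and 6 are fitted separately or together. Aim 3, by contrast, has time as Level 1 within participant, with a random intercept and slope for each person. Aim 2 reuses the Aim 1 model for the outcomes collected at every time point.

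**The concern.** Full information maximum likelihood helps with a missing outcome only when the likelihood contains something else about that person that predicts it, beyond the covariates already conditioned on. Here the obvious candidate for a missing month-6 value is the month-3 value of the same outcome. The Aim 1 model as listed gives month 3 no route to inform month 6, so the benefit claimed in the Missing Data section does not follow for missing primary outcomes.

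At stake is the primary comparison. If people doing poorly at month 3 leave one cohort more often than the other, the month-6 contrast is biased even though the trial holds the month-3 data that would correct it.

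**Working it through.** **Plan figures.** The plan gives no figure for missing outcomes. The one plan figure used below, as a yardstick, is the target effect of 0.30 SD. Its stated sample size of 352 reproduces: a two-sided 5% t-test with 80% power needs 176 per group, and 2 × 176 = 352.

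**Reading 1: separate fits at months 3 and 6.** Write A for treatment and Y0, Y3, Y6 for the outcome at baseline and months 3 and 6. The month-6 likelihood factors as f(Y0 | A) × f(Y6 | Y0, A). The treatment effect sits in the second factor. For a participant with Y6 missing, that factor integrates to 1, so the person contributes nothing to the effect. A center random intercept does not change this. With month 3 included, the likelihood is f(Y0 | A) × f(Y3 | Y0, A) × f(Y6 | Y3, Y0, A), and a participant seen at month 3 but not at month 6 does contribute.

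Two simulations used the article's cohort sizes (226 and 172). Everything else was assumed, and clustering was ignored. In both, month-6 dropout depended on the month-3 score in Cohort 1 only.

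| | Simulation A | Simulation B |
|---|---|---|
| Runs | 4,000 | 1,500 |
| True effect (SD) | 0 | 0.30 |
| Correlation baseline–month 3 / baseline–month 6 / month 3–month 6 | 0.6 / 0.6 / 0.7 | 0.6 / 0.5 / 0.6 |
| Log odds of dropout per SD of month-3 score (absolute) | 0.8 | 0.9 |
| Month-6 missing, Cohort 1 / Cohort 2 | 27% / 35% | 23% / 35% |
| Complete-case ANCOVA, mean (SD) | 0.066 (0.096) | 0.356 (0.103) |
| Likelihood on pretest + month 6 only | not run | 0.356 (0.103) |
| Joint likelihood with month 3, mean (SD) | −0.002 (0.092) | 0.301 (0.101) |

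- Complete-case bias: A, 0.066 − 0 = 0.066; B, 0.356 − 0.30 = 0.056. Against the 0.30 target these are 0.066/0.30 = 22% and 0.056/0.30 = 19%.
- Monte Carlo error: A, 0.096/√4,000 = 0.0015; B, 0.103/√1,500 = 0.0027. Both biases are well beyond it.
- In B, the likelihood fit to pretest and month 6 agreed with complete-case ANCOVA in every run, the largest difference being 9 × 10⁻⁹. This is the factorisation above, seen numerically.

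**Cases where the per-visit model does well.** Simulation B was repeated with Cohort 1 dropout depending on baseline instead, and with 10% of pretests missing at random (true effect 0.30). Complete case gave 0.296 (SD 0.116), likelihood on pretest + month 6 gave 0.304 (0.112), and the joint model gave 0.299 (0.106). None is materially biased, and likelihood gains some precision by keeping people without a pretest. In A with dropout completely at random, the SDs were 0.097 (complete case) and 0.092 (joint), a gain of 0.005/0.097 = 5%.

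**Reading 2: both visits pooled in the two stated levels.** Given center and covariates, a person's two values are then treated as independent. Month 3 still cannot inform a missing month 6, and the within-person correlation is left out. As an illustration, the correlation of the two visits after baseline adjustment is ρ = (r36 − r03·r06)/√[(1 − r03²)(1 − r06²)].

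- A's correlations: (0.7 − 0.36)/0.64 = 0.53.
- B's correlations: (0.6 − 0.30)/√(0.64 × 0.75) = 0.43.

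For an effect averaged over two observed visits, the true standard error is about √(1 + ρ) times the model-based one: √1.53 = 1.24 and √1.43 = 1.20. Robust standard errors clustered on participant or center would address this, but the article does not say at which level they apply. They would not restore the link from month 3 to month 6.

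**The case against.** The strongest reply has four parts.

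1. The Missing Data section serves all aims. In Aim 3, with time nested in participant, likelihood estimation does what that section says. This stands: the sentence is not false for the plan as a whole. The mismatch is confined to Aim 1 and the Aim 2 outcomes that borrow its model.
2. Change over time with pretest as a covariate may simply mean change conditional on baseline. That is a fair reading, but it is then the per-visit model, where a missing outcome gains nothing. The Aim 1 text also claims freedom from sphericity assumptions because covariance components are estimated. That is a repeated-measures property which the listed levels do not supply.
3. The month-3 score could be used as an auxiliary variable, a detail an analysis plan may hold. It could. But the article itself fixes the levels, the covariates and the missing-data method, and it claims the benefit. As written they do not fit together.
4. The size is assumed. This stands. The simulated bias comes from two chosen scenarios with dropout related to month 3 in one cohort only. Similar dependence in both cohorts would tend to offset in the contrast.

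A reader might go further in three ways that the documents do not support.

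- *Aim 1 has no participant level.* Level 1 is labelled the participant level. What is missing is an occasion level below it, or a participant random effect.
- *The protection is wholly absent.* People with missing pretests or covariates can be retained, and complete-case ANCOVA is unbiased when dropout depends only on modelled covariates.
- *Non-graduation gives the month-6 loss.* It was 62/226 = 27% in Cohort 1 and 61/172 = 35% in Cohort 2. Graduation is program completion, whereas data collection is compensated per event. Cohort 2 began six months later and finished at about month 12, so its figure includes losses after month 6. Rates near these were inputs to the simulations and are not evidence about month 6.

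**Conclusion.** The point holds in limited form. For a missing Aim 1 outcome, the method named in the Missing Data section adds nothing under the model listed for Aim 1 if the visits are fitted separately. If they are pooled in the two stated levels, within-participant correlation is ignored. The two sections need to be reconciled.

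The consequence depends on the dropout mechanism. It is nil for bias if dropout depends only on modelled covariates. It is about 0.05 to 0.07 SD, roughly a fifth of the 0.30 target, if month-6 dropout in one arm depends on the month-3 score as assumed above. Those values rest on assumed correlations, dropout strength and dropout rates, with clustering ignored. The article reports no month-6 missingness, so the actual size cannot be stated, and nothing here shows that the trial's estimate is biased. The change is worth making because it is cheap and uses data already collected.

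**What to change.** For each Aim 1 outcome, fit months 3 and 6 in one likelihood-based model with:

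- visit-by-treatment effects;
- within-participant covariance (or a participant random effect);
- a random intercept for center;
- baseline adjustment.

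Include all randomised participants with any post-baseline value. Report the contrasts at the time points the plan already names. Whether one of them should be the sole primary contrast is a separate choice that this point does not settle. Apply the same structure to the Aim 2 outcomes that use the Aim 1 model.

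Replace "Missing data will be imputed using full information maximum likelihood" with a statement that missing data are handled by full information maximum likelihood under missing at random, since the method does not fill in values.

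The cost is revised wording and a slightly larger model, with no new data. The article reports that preliminary analysis is under way, so the change should be dated and recorded before the Aim 1 comparisons are examined.

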#### Statistical Models

##### Aim 1

Primary outcome data will be analyzed in Aim 1. For each of the 3 outcomes in Aim 1 (Dietary Quality Score and Food Security), at 3-month and 6-month periods, a 2-level multilevel model (MLM) will be constructed that examines change over time for individual participants within centers. MLMs consider that participants within a cluster (eg, a center) share characteristics that make them more like each other than participants at other centers. MLM has several distinct advantages over other modeling strategies: (1) MLM has greater statistical power given that the estimated standard errors are corrected for model dependency; (2) there is no need to assume or test for the homoscedasticity or sphericity assumptions, as these variance and covariance components are estimated within the MLM model. Depending on model complexity and whether the statistical assumptions are met, the models will be estimated via Bayesian estimation or maximum likelihood estimation with robust standard errors. For Level 1 (participant level), the outcome variable of interest will be modeled using pretest score on the outcome measure, treatment status (ie, control or experimental), and any nonequivalent baseline participant characteristics as covariates. Level 2 (center level) will model the cluster effect of centers on outcomes.

##### Aim 2

Data collected for Aim 2 represent our secondary research questions (eg, physical activity, technology knowledge and attitudes, social isolation, and loneliness). Data collected at all time points (Physical Activity Scale for the Elderly [PASE], technology knowledge and attitudes, social isolation, and loneliness) will be analyzed using MLM described in Aim 1. To minimize participant fatigue, data for this secondary research aim will be collected at defined intervals (T0, T1, and T2). These data will include the Healthy Eating Index and Short Physical Performance Battery (SPPB) to assess physical function. Differences between groups will be assessed at T2 for each outcome via 2-level covariate MLM models. Level 1 (participant level) will test whether treatment status (ie, control or experimental), pretest score on dietary quality, and food security, and any nonequivalent baseline participant characteristics predict outcomes. At Level 2 (center level), we will model the influence of the 7 centers.

##### Aim 3

To assess the long-term impacts of the program at T3, Level 1 (time) will model the change in the outcome variables throughout the study (T0, T1, T2, and T3) within each participant. Specifically, each participant’s random intercept (eg, initial status) and the random slope over the 3 time periods will be calculated, and the time variable will represent the change in a particular outcome variable (ie, food security) over time within each participant. Level 2 (time nested within participant characteristics) will test whether treatment status (ie, control or experimental) and any nonequivalent baseline participant characteristics predict outcomes. If the ICC coefficient is greater than 0.10, a third level will be added to the model to control for clustering by center. Finally, participants will be clustered within centers (Level 3).

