## Methods

### Design

This study is a closed cohort stepped wedge design in which the timing of the intervention is randomized by cluster, with the sequential crossover of clusters from control to intervention until all clusters have received the intervention. With this design, each cluster contributes data when they are participating in the intervention and when they are not. Stepped wedge designs are useful for several reasons. First, they allow all participants to receive the intervention, and each intervention arm can serve as its control, which decreases the number of units needed. Second, the design is practical in a situation with limited resources where the intervention logistically cannot be carried out all at once. Third, the design allows researchers to examine any effects of time on the intervention’s effectiveness [36,37]. Baseline data on current dietary intake, food security, malnutrition, technology use and attitudes, physical activity, social isolation, loneliness, and demographics were collected from all participants at Time 0. Each of the 12 centers was randomly assigned to one of 2 cohorts. Participants in Cohort 1 received the intervention first. Once Cohort 1 participants finished the intervention, a crossover occurred as Cohort 2 participants began the intervention. At the 12-month time point, the second cohort completed the intervention. Data will be collected for both groups each time point from T0 to T3 (Figure 1).

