#### Randomization and Allocation

Twelve out of the 14 centers participated in the study and were stratified by congregate meal participant enrollment and attendance as large (>100 participants), medium (50‐100 participants), and small (<100 participants) and randomly assigned to one of 2 start times: immediately (Cohort 1) or 6 months later (Cohort 2). Site randomization by a statistician occurred after participant recruitment; however, the treatment condition was not revealed to the participants. Neither the study participants nor the study staff were blinded to the treatment conditions.

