## Results

The project was funded in October 2022. As indicated in the study progress (Figure 3), recruitment and screening started in June 2022. The research team recruited and screened 150 participants by the end of August 2022 at the 7 original target centers. Due to the low recruitment numbers, the number of centers and recruitment time were extended. Seven additional centers for recruitment were incorporated starting in September 2022. Power analysis was completed to ensure adequate recruitment numbers were met with the 14 centers. NIH was notified in writing of these changes. Fourteen centers were condensed to 12 centers (1 closed because of structural damage and 1 smaller center merged with a larger sister center).

A total of 578 older adults completed the screening, of whom 507 participants were eligible to participate in the study (88%). The 12 centers were randomly assigned into 2 study cohorts, which consisted of a total of 398 older adult participants. Cohort 1 consisted of 226 eligible participants, of whom 164 participants graduated from the program. Cohort 2 had 172 eligible participants, of whom 111 participants graduated from the program (Figure 4). Monthly bingo and informative presentations (nonnutrition and nonphysical activity–related) were conducted with Cohort 2 centers for engagement and retention. Focus groups were conducted for Cohort 1 postintervention in October 2023 and for Cohort 2 in June 2024 to assess the fidelity of the intervention. Data collection for Cohort 2 is currently ongoing. Preliminary data analysis is being conducted for all cohorts to evaluate the intervention’s outcomes.

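### Robust standard errors on 12 randomized centers, with no small-sample correction named, make the primary test anticonservative; one estimator with small-sample inference should be fixed

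*Protocol article*

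**What the plan says.** Under Statistical Models, Aim 1, the article sets out a two-level model for diet quality and food security at 3 and 6 months. Participants are level 1, with pretest score and treatment status as predictors. For level 2, "Level 2 (center level) will model the cluster effect of centers on outcomes". On estimation, "the models will be estimated via Bayesian estimation or maximum likelihood estimation with robust standard errors", the choice depending on how complex the model is and whether its assumptions hold. No reference distribution, degrees-of-freedom method or small-sample version of the sandwich is named.

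On the number of clusters, the Design section says "Each of the 12 centers was randomly assigned to one of 2 cohorts", and Randomization and Allocation agrees: "Twelve out of the 14 centers participated in the study". Cohort 2 starts 6 months after Cohort 1. The Results section adds that "Preliminary data analysis is being conducted for all cohorts to evaluate the intervention’s outcomes".

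**The concern.** A center-level sandwich variance is justified when there are many clusters. Here the whole treatment comparison at 3 and 6 months is between two sets of centers, because no center has yet contributed both conditions. The later crossover therefore adds nothing to this contrast, and the information about treatment comes from 12 units, however many participants each holds.

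With so few units the uncorrected sandwich understates the variance of the treatment effect. If the statistic is then referred to the normal distribution, a second error in the same direction is added. Confidence intervals for both primary outcomes would be too narrow and p-values too small. The plan also leaves open which of two inferential frameworks will carry the primary result, while outcome data are already being analysed.

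**Working it through.** **Inputs from the article**
- Clusters: 12 centers, 2 cohorts (Design; Randomization and Allocation). Aim 2 still speaks of 7 ("At Level 2 (center level), we will model the influence of the 7 centers"), the number of original target centers; 12 is used here.
- Participants: 398 ("which consisted of a total of 398 older adult participants"), of whom 226 are in Cohort 1 ("Cohort 1 consisted of 226 eligible participants, of whom 164 participants graduated from the program") and 172 in Cohort 2, with 111 graduates there.
- ICC 0.016 and alpha 0.05 (Power Calculations).
- Pretest score as covariate (Aim 1).

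**Assumed, because the article does not give them:** two-sided testing, a 6:6 split of centers, individual center sizes, normal outcomes, a pretest slope of 0.5, and other ICCs from 0 to 0.10.

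**The plan's own figures.** The article states no type I error for its analysis, only the nominal 0.05 behind its sample size. That level is confirmed: n per group = 2(z0.975 + z0.80)²/d² = 2(1.960 + 0.842)²/0.30², which rounds up to 175, or 350 in total against the stated 352. Power at d = 0.41 with 374/2 = 187 per group is 97.75%, against the stated 97.7%.

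**Step 1: degrees of freedom.** Centers minus cohort means: 12 - 2 = 10.

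**Step 2: the reference distribution alone.** If the standard error were unbiased and the statistic followed t on 10 df, a cut-off of 1.96 would reject P(|t10| > 1.96) = 7.8%.

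**Step 3: adding the sandwich bias.** Null trials were simulated with N = 398 (226/172), a random-intercept model fitted by ML, pretest adjustment and a center-level sandwich. There were 3,000 trials per setting (1,500 for the bias-corrected column), so the Monte Carlo error is at most about √(0.12 × 0.88/3000) = 0.6 points. Near-equal centers had 37-38 and 28-29 participants. Unequal centers had 70, 55, 40, 30, 20, 11 and 55, 42, 30, 22, 14, 9. Rejection at nominal 5%:

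| ICC | Centers | Uncorrected, z | Uncorrected, t10 | K/(K-1) factor*, t10 | Mancl-DeRouen, t10 |
|---|---|---|---|---|---|
| 0 | near-equal | 10.4% | 6.7% | 5.6% | 3.1% |
| 0.016 | near-equal | 10.3% | 6.4% | 5.6% | 4.1% |
| 0.05 | near-equal | 10.7% | 7.0% | 5.9% | 4.0% |
| 0.10 | near-equal | 10.2% | 6.9% | 5.5% | 3.1% |
| 0 | unequal | 11.9% | 8.3% | 7.0% | 3.8% |
| 0.016 | unequal | 12.4% | 9.0% | 7.7% | 4.5% |
| 0.05 | unequal | 12.6% | 8.8% | 7.6% | 4.1% |
| 0.10 | unequal | 11.3% | 7.6% | 6.4% | 3.5% |

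*Also multiplied by (N-1)/(N-p) = 397/395, which is negligible.

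With only the 164 + 111 = 275 graduates, unequal centers and ICC 0.016, the uncorrected sandwich rejects 11.1% with z and 7.5% with t10.

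**Step 4: REML with model-based errors.** Simulations without the pretest covariate (12 centers, 6:6, mean size 33, 6,000 trials per setting, equal sizes or size CV 0.5) gave:

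| ICC | ML, robust, z (equal / CV 0.5) | REML, model-based, t10 (equal / CV 0.5) |
|---|---|---|
| 0.016 | 10.1% / 11.8% | 3.5% / 3.9% |
| 0.05 | 10.0% / 11.2% | 4.5% / 5.0% |
| 0.099 | 9.8% / 11.5% | 4.5% / 5.2% |

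**Step 5: is ML the culprit?** With the same uncorrected sandwich and z, ML and REML reject 10.2% and 10.2% (ICC 0.016, equal sizes), 11.2% and 11.1% (ICC 0.016, CV 0.5), and 10.8% and 10.8% (ICC 0.10). The variance component enters only through the weights, so it barely matters here. It does matter for model-based errors: ML with t10 rejected 6.6-7.8% at ICC 0.05-0.10 in the Step 3 settings.

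**The case against.** The strongest reply is that the article does not specify the procedure that gives 10-12%. It names no reference distribution and no sandwich version, and a bias-corrected sandwich with t on 10 df, which rejects at or below 5%, is also ML with robust standard errors. An analysis plan that is not shown may supply that detail. This stands to an extent: a reader might infer that the plan doubles the type I error, and the article does not support that without the added assumptions of a normal reference and no correction. What remains is that the named method, in its ordinary uncorrected form, stays above nominal even with t on 10 df. The simple K/(K-1) factor does not cure it when centers differ in size, as the article's large, medium and small strata suggest they do.

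A reader might also blame maximum likelihood itself. Step 5 shows that this is wrong while robust errors are used.

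Finally, a reader might see the choice between Bayesian and ML estimation, alongside preliminary analyses, as a route to a favourable result. The documents do not show that. The stated criteria are model complexity and assumptions, not the estimated effect, and nothing says that the estimator is being chosen from outcome results. Nor is the Bayesian route shown to be invalid. The supportable remark is only that the framework is left open when it could be closed.

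**Conclusion.** The concern holds in a conditional form. For a contrast resting on 12 centers, the uncorrected sandwich rejects about 10-12% of null trials with a normal reference and about 6.5-9% with t on 10 df, against a nominal 5%. The causes are the downward bias of the sandwich and the reference distribution.

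The inflation appeared at every ICC from 0 to 0.10 and for both size patterns, so it does not hinge on the assumed 0.016. It does rest on the 6:6 split, the assumed center sizes and normal outcomes. Food security is a short count score, so its exact rates may differ. Using 7 centers, as the Aim 2 text has it, would be expected to make the inflation larger.

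**What to change.** Name one primary estimator, with its small-sample inference, for both primary outcomes. Either of these would serve:

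- a random-center model fitted by REML, with model-based standard errors and Kenward-Roger, Satterthwaite or t on 10 df (3.5-5.2% in Step 4, where t on 10 df was used);
- if robust errors are kept, a bias-corrected sandwich such as Mancl-DeRouen with matching degrees of freedom (4.1-4.5% at ICC 0.016, 3.1-4.5% over all settings).

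Make Bayesian estimation a sensitivity analysis, so that the primary framework is settled independently of the outcome data. Correct the center count in the Aim 2 text at the same time.

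The cost is analysis wording; both methods are in standard software, and no data or participants are added. Intervals will be wider: the change of reference alone multiplies the half-width by 2.228/1.960 = 1.14, and the bias correction adds to that. At some ICCs the corrected tests are slightly conservative, which costs a little power.

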**Methods:**

This proposed digital nutrition education intervention study targets technologically limited older adults enrolled in the congregate meal program (CMP) using a stepped-wedge clustered randomized controlled trial. Key community partners, City of San Antonio Department of Health Services Senior Services Division and OATS, contributed to the study’s planning phase, research design, and implementation. The 20-week intervention included 5 weeks of in-person technology training, including internet access and technical support for 1 year and devices, followed by 15 weeks of a culturally tailored online nutrition education intervention. The study randomized 398 older adults from 12 congregate meal sites. Data collection took place at baseline, 3 months, 6 months, 9 months, 12 months, and 18 months. If successful, the impact of this program could be applied throughout the national OATS network and to similar CMPs to bridge the digital divide beyond the COVID-19 pandemic.

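### Aim 2 sends data from all visits to a model with no calendar-time term; read literally, this confounds treatment with time after crossover, and the nearby T2 sentence does not settle whether that reading is meant

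*Protocol article*

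**What the plan says.** The Design section of the Protocol article describes the trial thus: "This study is a closed cohort stepped wedge design in which the timing of the intervention is randomized by cluster". Centers move one way, from the control condition to the intervention, so that in the end every center is treated. Under Randomization and Allocation, the 12 centers are "randomly assigned to one of 2 start times: immediately (Cohort 1) or 6 months later (Cohort 2". The abstract gives the visits: "Data collection took place at baseline, 3 months, 6 months, 9 months, 12 months, and 18 months".

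Under Statistical Models, Aim 1 is set "at 3-month and 6-month periods, a 2-level multilevel model (MLM) will be constructed that examines change over time". At the participant level the outcome "will be modeled using pretest score on the outcome measure, treatment status (ie, control or experimental), and any nonequivalent baseline participant characteristics as covariates". The second level is a center effect. No period or visit term is listed, and there is no level for visits within a participant.

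Aim 2 then states: "Data collected at all time points (Physical Activity Scale for the Elderly [PASE], technology knowledge and attitudes, social isolation, and loneliness) will be analyzed". The model named for this is the one set out under Aim 1. Table 2 confirms that these measures are taken at every visit. A few sentences later, after the text on the Healthy Eating Index and the Short Physical Performance Battery (SPPB), Aim 2 says that group differences will be tested at T2. The article does not say which month T2 is. Only Aim 3 has an explicit time variable and a within-participant level.

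**The concern.** In a stepped wedge trial the treated share of the data rises with calendar time by design. A model that pools visits from before and after crossover must therefore adjust for time, or the treatment coefficient takes up part of any change that would have occurred anyway. Aim 1 avoids this by stopping at month 6. Aim 2 borrows the Aim 1 model but, as worded, not its time window.

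The outcomes at stake are physical activity, technology knowledge and attitudes, social isolation and loneliness. Drift in at least one of these is plausible on the article's own account: the Technology Intervention section notes a marked rise in older adults' internet use over recent years. The Design section also presents the study of time effects as an advantage of the stepped wedge, yet the model assigned to these outcomes has no term for time. In addition, if visits are stacked without a participant level, repeated measurements on one person are treated as independent within a center.

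**Working it through.** **Scale.** The article gives no figure for this bias, so there is none to reproduce. Its power section supplies the yardstick of 0.30 SD. Its stated power checks: with effective N = 374 (187 per group) and effect 0.41, z = 0.41 × √(187/2) − 1.96 = 2.00, which gives 97.7% as stated.

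**Which visits are treated** (start at month 0 for Cohort 1 and month 6 for Cohort 2; the month-6 visit in Cohort 2 counts as control):

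| Month | 3 | 6 | 9 | 12 | 18 |
|---|---|---|---|---|---|
| Cohort 1 | treated | treated | treated | treated | treated |
| Cohort 2 | control | control | treated | treated | treated |

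Mean month of control rows: (3 + 6)/2 = 4.5. Mean month of treated rows with equal cohorts: (3 + 6 + 9 + 12 + 18 + 9 + 12 + 18)/8 = 10.9.

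**Inputs for the bias.** 12 centers, 6 per cohort (equal split assumed); 33 participants per center (398/12 ≈ 33); ICC 0.016 from the power section; true effect 0; linear trend of 0.01 or 0.02 SD per month, which is an assumption. No dropout is assumed, and the pretest covariate is not modeled.

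**Formula.** On center-by-visit means, with design matrix X (intercept and treatment status) and month vector m, the expected coefficients per unit of monthly trend are (ΣXᵀV⁻¹X)⁻¹ ΣXᵀV⁻¹m. Here V = 0.016·J + (0.984/33)·I, where J is the all-ones matrix and I the identity. This is the written model's variance: a center effect, with visits otherwise independent.

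**Result for treatment status.**

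| Visits pooled | Multiplier | Bias at 0.01 SD/month | Bias at 0.02 SD/month |
|---|---|---|---|
| 3, 6 | 0 | 0 | 0 |
| 3 to 12 | 5.18 | 0.05 | 0.10 |
| 3 to 18 | 7.79 | 0.08 | 0.16 |

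**Hand check.** Ignoring centers, the months 3-18 multiplier would be 10.9 − 4.5 = 6.4. Using only Cohort 2's before-after change it would be (9 + 12 + 18)/3 − 4.5 = 8.5. A random center intercept lies between the two, as 7.79 does. For months 3-12 the limits are 8.5 − 4.5 = 4.0 and 10.5 − 4.5 = 6.0, and 5.18 lies between them.

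**Relative size.** The model standard error for months 3-18 is 0.062 SD. At 0.02 SD per month the bias is 0.156/0.062 = 2.5 standard errors and 0.156/0.30 = 52% of the design effect size. For months 3-12 it is 0.104/0.30 = 35%.

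**Sensitivity.** With the reported cohort sizes (226 and 172) the multipliers are 5.08 and 7.70. Adding a within-person correlation of 0.5 (assumed) gives 5.65 and 8.22.

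**After adding categorical visit effects.** The multiplier is 0 for every set of visits. A full treatment-by-visit model over months 3-18 has 10 columns but rank 7: at months 9, 12 and 18 everyone is treated, so no separate effect can be estimated there.

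**The case against.** The strongest counter-argument is that the phrase about all time points names a class of outcomes, not an analysis window. Table 2 separates measures taken at every visit from those tied to the assigned cohort's intervention, and Aim 2 follows the same split. The two Aim 1 outcomes carry the same every-visit label in Table 2, yet Aim 1 analyzes them only at months 3 and 6. Borrowing the Aim 1 model may mean borrowing its window too. With participants at Level 1 and the pretest as a covariate, the model also looks like one row per participant fitted separately at each visit. The T2 sentence points the same way if T2 is month 6, and Aim 3 already provides a longitudinal model with time and participant effects. Under any of these readings no post-crossover data enter the contrast and the bias vanishes.

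This stands as a plausible reading, and it rules out a flat claim that the Aim 2 estimates will absorb drift. It does not remove the point. The T2 sentence follows the Healthy Eating Index and SPPB text; if it also governs the other outcomes, it conflicts with the statement that data from all time points go into the model. The description of Aim 1 as examining change over time does not supply a time term either, because the listed covariates contain none and Aim 3 names time where it is intended.

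A reader might also infer that the primary analysis is affected, or that recovery from pandemic closures produced a trend of this size. The documents support neither. Aim 1 compares the cohorts before crossover, and the closures are described for the earlier pandemic period, not for follow-up.

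**Conclusion.** The point holds in conditional form. Followed literally, Aim 2 applies a model without a time term to visits on both sides of the crossover and so confounds treatment with calendar time. Under the assumed trends, the bias for a null effect is about 0.05 to 0.10 SD when months 3-12 are pooled and 0.08 to 0.16 SD when months 3-18 are pooled. It is zero at months 3 and 6. Its sign and size follow the unknown trend, so these figures show sensitivity and do not predict the result.

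The article does not say clearly which reading is meant. The all-time-points sentence and the T2 sentence must be reconciled, and T2 tied to a month. The matter is confined to the Aim 2 outcomes measured at every visit; the Aim 1 comparison is not biased by the missing time term.

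**What to change.** State which visits enter the Aim 2 treatment contrast, map T0 to T3 to months, and adopt one of two analyses.

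1. Restrict the contrast to months 3 and 6, as in Aim 1. This needs only a wording change and removes the confounding. It gives up the later data: the standard error is about 0.114 SD with the reported cohort sizes and an assumed within-person correlation of 0.5.
2. If later visits are pooled, model visits within participants within the 12 centers, with visit as a categorical fixed effect, a single time-varying treatment effect, participant and center random effects, and the baseline value. Do not specify treatment by visit, which cannot be estimated after month 6. A single effect assumes that the benefit does not change with time since start, and this should be stated.

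The price of option 2 is precision. For months 3-18 with 33 per center, adding visit effects raises the standard error from about 0.062 to 0.084 SD under the written model's independent-visit variance. With an assumed within-person correlation of 0.5 and the reported cohort sizes, it rises from 0.048 to 0.063. The narrower interval is not a real gain, because it is centered on a biased estimate whenever there is a trend. No further data collection is needed.
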